**New fact**

Any new safety information that may lead to a reassessment of the risk-benefit ratio of the study, or which may be enough to consider making changes to the performance of the research.

## X - 2 - Adverse events

The adverse events that may occur during the study are mainly related to the treatments used.

- Main adverse events related to the education programme
  - No known or reported evidence on this subject
- Main adverse events related to the exercise programme
  - Increase in pain related to exercise
  - Muscle, ligament and joint injuries related to exercise
  - Decompensation of arterial or cardiac condition during exercise

## X - 3 - SERIOUS ADVERSE EVENT MANAGEMENT PROCEDURE

As this is a biomedical research study classified as “risk A”, i.e. for which there is a negligible **additional risk expected from the research**, no serious adverse events are expected through the course of the research.

Furthermore, there cannot be any suspected unexpected serious adverse reactions (SUSARs) related to the research.

In these conditions:

- The investigator will not be expected to declare any serious adverse events occurring during the research to the sponsor. Should such events occur, these will be related to the patient’s condition or their therapeutic treatment in the context of care, and will not be related to the research.

- It is not considered necessary to include a serious adverse event reporting form or an adverse event classification table with the protocol.

- It is not considered necessary to create an independent monitoring committee.

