## I - 5 - Expected benefits and risks

A short spa therapy programme, if shown to be effective, would allow the duration of sick leave to be reduced in patients with lower back pain.

There are no expected risks.

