2. With regard to methodology, the limitations of the Zelen method are the risk of contamination through refusal to undergo the intervention (short spa therapy programme). In the Thermarthrose study (Forestier R, ARD 2009), a large-scale, multi-centre trial assessed a specific treatment involving spa therapy vs standard treatment according to a Zelen method, with a 10% rate of contamination. The risk of contamination should be no higher in our study, taking into account:
   1. the lack of risk of the intervention;
   2. the lack of other treatments available;
   3. the duration of the intervention, which will be shorter;
   4. the patients who are on sick leave.

The risk of contamination in the standard-care group is highly unlikely, given that the short spa therapy programme is not currently offered outside this study.

Another risk of the Zelen method is the hypotheses being unblinded for patients. This risk is minimal, as the endpoint assessment visits (at M3, M6 and M12) will be done by post or email (or by phone, if no response is received), which prevents the patients from the two groups from being in contact with each other.

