## IX -1- 7- Tolerance

Adverse events

Adverse events will be described per treatment group according to their MedDRA codes (SOC and PT) and according to their intensity and imputability to the treatment. The proportion of subjects with at least one adverse event will be compared between the groups using the Chi-squared test or Fisher’s exact test.

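### Section X-3 presumes in advance that no serious adverse event will be related to the research, contradicting X-2 and pushing the planned imputability description towards unrelated

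*Protocol*

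**What the plan says.** Section X-3 classifies the study as risk A, expects no SAEs, and rules out any suspected unexpected serious adverse reaction related to the research. From this it draws three consequences:

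- "The investigator will not be expected to declare any serious adverse events occurring during the research to the sponsor". The reason given is that the cause would be the underlying illness, or else "their therapeutic treatment in the context of care, and will not be related to the research".
- The protocol carries neither a form for reporting SAEs nor a table for classifying adverse events.
- No independent monitoring committee is needed.

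Other sections bear on the same matter:

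- **I-5:** "There are no expected risks".
- **X-2:** adverse events are expected to arise mainly from the treatments used. For the exercise programme it lists increased pain, muscle, ligament and joint injuries, and "Decompensation of arterial or cardiac condition during exercise".
- **X-1:** an event is serious if, among other criteria, it is life-threatening or involves hospitalisation. For research without a listed health product, the section defines a category of adverse event due to the research.
- **III-4 (justification of the modified Zelen method):** "the short spa therapy programme is not currently offered outside this study".
- **VII-2:** spa physicians fax a report of any AEs and SAEs occurring during therapy to the Clinical Research Unit.
- **VIII-2:** the eCRF is to contain an SAE form.
- **IX-1-7:** adverse events are described by group "according to their intensity and imputability to the treatment". In addition, "The proportion of subjects with at least one adverse event will be compared between the groups".

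**The concern.** Relatedness is a judgement made on the facts of each event. X-3 gives the answer in advance and in one direction. That answer conflicts with the list in X-2 just before it, where the trial's own exercise sessions are given as the source of events that can be serious.

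The safety conclusion is at stake. If assessors take X-3 at its word, serious harm from the programme may be filed as background disease or routine care. A report of no spa-related SAEs would then partly reflect the presumption. There is little independent check: X-3 dispenses with a monitoring committee, and X-4 gives oversight of tolerance to a steering committee that includes the project's initiators and the sponsor's representatives.

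**Working it through.** **1. The passages side by side**

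| Question | X-3 | Elsewhere in the protocol |
| --- | --- | --- |
| Can the intervention cause a serious event? | No: the cause is the disease or routine care | X-2: cardiac or arterial decompensation is a main event of the exercise programme; X-1 would class a life-threatening case, or one involving hospitalisation, as serious |
| Is the programme part of routine care? | Only treatment given as care is accepted as a cause | III-4: the programme is not offered outside the study |
| Is any risk expected? | No SAE expected (I-5 expects no risks at all) | X-2 lists expected types of harm |
| Is causality assessed? | Stated in advance | IX-1-7: described by imputability |
| Are SAEs recorded? | Not declared to the sponsor; no form with the protocol | VII-2: reported to the Clinical Research Unit; VIII-2: SAE form in the eCRF |

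The first three rows are contradictions about cause. The fourth is a tension between a presumption and a planned assessment. The fifth concerns recording and shows that SAEs do reach the data.

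**2. The plan's own figure**

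The protocol states no SAE rate, so there is no safety figure to reproduce. The only input used below is the planned spa arm of 350 (Summary).

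**3. Illustration: what unprejudiced assessment could show**

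Let p be the true risk of a spa-related SAE (assumed). Expected events are 350p, and P(at least one) = 1 − (1 − p)^350.

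| Assumed p | Expected events | P(at least one) |
| --- | --- | --- |
| 0.1% | 0.35 | 30% |
| 0.5% | 1.75 | 83% |
| 1% | 3.5 | 97% |
| 2% | 7 | 99.9% |

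If 10% declined the spa (the contamination rate that III-4 cites from an earlier spa trial), 315 would be treated. At p = 1% the probability is then 1 − 0.99^315 = 96%.

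With 0 events in 350, the exact one-sided 95% upper bound on p is 1 − 0.05^(1/350) = 0.85%.

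**4. Illustration: the effect of a push towards unrelated**

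Suppose a share s of truly related SAEs is recognised as related (s is assumed; nothing in the protocol fixes it). Then P(at least one recorded as related) = 1 − (1 − sp)^350, and the bound on p from a zero count becomes 0.85%/s. At p = 1%:

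- s = 1: probability 97%, bound 0.85%.
- s = 0.5: sp = 0.5%, probability 83%, bound 0.85%/0.5 = 1.7%.
- s = 0.1: sp = 0.1%, probability 30%, bound 0.85%/0.1 = 8.5%.

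Since s would not be known, the reader could not tell which bound applies.

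**5. Can the between-arm comparison make up for this?**

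The comparison of any adverse event in IX-1-7 does not depend on attribution. Suppose 1% of spa patients had a related SAE and no other event, so that the spa proportion is one point above the control proportion b. With 350 per arm, z = 0.01/√{[b(1 − b) + (b + 0.01)(0.99 − b)]/350}, and power ≈ Φ(z − 1.96) + Φ(−z − 1.96).

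- b = 5%: z = 0.58, power about 9%.
- b = 20%: z = 0.33, power about 6%.

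Both values of b are assumed. The comparison is protected from the bias but has little chance of showing an effect of this size.

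**The case against.** A reader might infer that the imputability table must show zero spa-related SAEs whatever the true risk, so that it carries no information. The documents do not support that, for four reasons:

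- The sentence explains why SAEs need not be declared to the sponsor. No section tells a physician, investigator or statistician to code imputability as unrelated.
- X-3 speaks of relation to the research, whereas IX-1-7 speaks of imputability to the treatment.
- VII-2 and VIII-2 still provide for recording SAEs, and X-2 openly names treatment-related events. A spa-related SAE can therefore be recorded and described as such.
- The comparison of any adverse event between arms has no causality filter.

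The first and third reasons stand and settle that a zero is not forced. The second stands only in part: the one treatment X-3 accepts as a cause is treatment given as care, and X-1 itself has a category of event due to the research. The fourth is true, but step 5 shows how little that comparison could reveal.

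It can also be said that III-4 mentions the programme's unavailability only to argue that contamination is unlikely, and that Annex III describes the pool movements as already in use at the centres. Calling the programme research rather than care is therefore an inference. It is a strong one for the programme as a whole, and the conflict with X-2 does not depend on it.

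**Conclusion.** The concern holds as a contradiction and a source of bias. X-3 asserts the cause of every SAE before any has occurred. X-2 says otherwise about the trial's own exercise programme, III-4 makes attribution to routine care hard to sustain, and I-5 and IX-1-7 do not fit with it either. An assessor following the protocol is pushed towards unrelated, so a report of no spa-related SAEs would be weak evidence of safety.

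The size of the bias cannot be derived from the protocol. The probabilities above rest on assumed risks, assumed recognition shares and, in step 5, assumed background proportions. They show what could be lost, not what will be. A statistical analysis plan could not fully repair this, because the problem is a positive statement in the protocol.

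**What to change.** 1. In X-3, delete the statement that decides in advance that SAEs are unrelated to the research, and review the adjoining exclusion of suspected unexpected reactions, which makes the same presumption.
2. State instead that the physician who reports an event on the existing AE/SAE reports (VII-2, VIII-2) judges its relation to the spa programme case by case, and that events of the kinds listed in X-2 are not presumed unrelated.
3. Reconcile I-5, VII-2, VIII-2, IX-1-7, X-2 and X-3, both on cause and on how SAEs are recorded and passed on. Which reporting rule should prevail is for the sponsor to settle.

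An exact upper confidence bound for the proportion with a related SAE would be useful, but it is optional and can be left to the statistical analysis plan.

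The cost is wording. The reports and the description by imputability are already planned, so no visits or staff are added. The downside is that the final safety statement may be less favourable.

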## X - 4 - STEERING COMMITTEE

The committee will be made up of the clinicians who initiated the project, the biostatistician in charge of the project, the sponsor’s representatives and the Clinical Research Unit (URC) appointed for this study.

It will define the general organisation and performance of the research and will coordinate the information. It will initially determine the methodology and decide over the course of the research what action must be taken in unforeseen situations, and will monitor the progress of the research, particularly with regard to tolerance and adverse events.

# XI – RIGHT TO ACCESS THE INFORMATION AND SOURCE DOCUMENTS

Individuals with direct access in accordance with the legislative and regulatory provisions in force, in particular Articles L.1121-3 and R.5121-13 of the French Public Health Code (e.g., researchers, individuals in charge of quality control, monitors, clinical research assistants, auditors and all individuals collaborating in clinical trials) will take all the necessary precautions in order to ensure the confidentiality of the information related to the investigational medicinal products, trials, individuals taking part in the research, and in particular any information involving their identity, as well as the results obtained. The data collected by these individuals through the course of quality controls or audits will then be made anonymous.

# XII – LEGAL AND ETHICAL ASPECTS

The sponsor is defined by Law 2004-806 of 9 August 2004. Before beginning the research, each investigator must provide the sponsor’s representative in the research with a signed and dated copy of their curriculum vitae, which must include their French National Medical Council registration number.

## XII - 1 - REQUEST FOR AUTHORISATION FROM THE ANSM

Before beginning the research, the sponsor must submit an authorisation request file to the competent authority (the ANSM, formerly Afssaps). The competent authority, as defined in Article L. 1123-12, makes decisions related to the safety of individuals taking part in a biomedical research study, taking into account the safety and quality of the products used during the research in accordance with the regulations in force, where applicable, their condition of use and the safety of individuals with regard to procedures carried out and the methods used, as well as the planned methods of patient follow-up.

## XII - 2 - REQUEST FOR ETHICS COMMITTEE OPINION

In accordance with Article L.1123-6 of the French Public Health Code, the sponsor must submit the research protocol to an Ethics Committee. The committee’s opinion will be reported to the competent authority by the sponsor before the research begins.

## XII - 3 - AMENDMENTS

The sponsor must be informed of any planned changes to the protocol by the principal investigator.

Amendments must be classified as substantial or non-substantial.

A substantial amendment is an amendment which may, in one way or another, change the guarantees given to the individuals taking part in the biomedical research (change in inclusion criteria, extension of enrolment period, participation of new sites, etc.).

Once the research has started, any substantial amendments on the sponsor’s initiative must receive a favourable opinion from the Ethics Committee and authorisation from the competent authority prior to being implemented. In this case, where necessary, the committee will ensure that a new consent form is duly collected from individuals participating in the research.

Moreover, any extension to the research (radical change in the treatment regimen or populations included, extension of treatments and/or therapeutic procedures not originally foreseen in the protocol) must be considered as a new research study.

Any substantial amendment must be submitted by the sponsor, after payment of the corresponding fee, for authorisation from the ANSM and/or for the Ethics Committee’s opinion.

## XII - 4 - CNIL DECLARATION

The law provides that the declaration of the electronic file with the personal data collected for the research must be prepared before the effective start of the research.

## XII - 5 - Information sheet and consent form

Written consent must be collected from any individual participating in the research before any procedures related to the biomedical research are performed.

Within the context of this study, the patients will be enrolled at the visit with the rheumatologist or the rehabilitation physician (enrolment visit). During this visit, the patient will be informed of all of the study-related information. At the end of the enrolment visit, if the patient meets all the eligibility criteria and agrees to participate in the study, he or she will provide the physician with the signed consent form.

## XII - 6 - FINAL REPORT ON THE RESEARCH

The final report on the research will be drafted by the principal investigator in collaboration with the biostatistician for this study. This report will be submitted to each of the investigators for their opinion. Once a consensus has been reached, the final version must be approved with the signature of each of the investigators and sent to the sponsor as soon as possible after the effective end of the study. A report prepared in accordance with the competent authority reference plan must be sent to the competent authority and to the Ethics Committee within one year after the end of the study. The end of the study is understood to be the last follow-up visit of the last subject enrolled. This period is set at 90 days if the research is terminated early.

# XIII – DATA PROCESSING AND STORAGE OF DOCUMENTS AND DATA RELATING TO THE RESEARCH STUDY

The documents from a research study falling under the scope of the law on biomedical research must be archived by all the parties for a period of 15 years after the end of the research (see GCP, chapter 8: essential documents).

This indexed archive consists of:

- Copies of the ANSM authorisation letter and the mandatory opinion from the Ethics Committee;
- Successive versions of the protocol (identified by the version number and date);
- Letters of correspondence with the sponsor;
- The consent forms signed by the subjects in a sealed envelope (in the case of minor subjects, these are signed by their parents or guardians) with the corresponding list or enrolment register;
- The complete and validated case report form for each subject enrolled;
- Any specific annexes to the study;
- The final study report from the statistical analysis and the quality control of the study (sent in duplicate to the sponsor);
- Certificates from any audits performed during the course of the research;

The database that gave rise to the statistical analysis must also be archived by the head analyst (hard copy or electronic copy).

# XIV – INSURANCE AND SCIENTIFIC COMMITMENT

## XIV - 1 - INSURANCE

AFRETH is the sponsor of the research. In accordance with the law on biomedical research studies, it has taken out an insurance policy with the company XX for the full duration of the research, guaranteeing its own civil liability as well as that of any intervening parties (physicians or staff involved in conducting the research) (Law no. 2004-806, Art. L.1121-10 of the French Public Health Code).

AFRETH reserves the right to interrupt the research at any given time for medical or administrative reasons. If this occurs, the investigator will be notified.

## XIV - 2 - SCIENTIFIC COMMITMENT

Each investigator undertakes to comply with the obligations of the law and to conduct the research in accordance with the GCP guidelines, complying with the principles set forth in the Declaration of Helsinki in force. To this end, a copy of the scientific commitment, dated and signed by the principal investigator of each clinical department of a participating site, will be provided to the sponsor’s representative.

A delegation of tasks form will be filled in, dated and signed by all the collaborators in the research.

# XV – RULES REGARDING PUBLICATION

# XVI – LIST OF ANNEXES

**Annex 1**: Bibliography references

**Annex 2**: Investigators and Associate Teams

**Annex 3**: Standardised therapy protocol

# ANNEX III – Standardised spa therapy protocol

1. Spa therapy programme (2 hrs/day)
2. Exercise programme (½ hr)
3. Group therapeutic education (45 mins)
   - Physical activity and rest
   - Work
   - Pain management
4. Back guide

**Distribution and content of the five sessions:**

| Times | **1st session** | **2nd session** | **3rd session** | **4th session** | **5th session** |
| --- | --- | --- | --- | --- | --- |
| **2 hrs**  **morning** | Spa therapy | Spa therapy | Spa therapy | Spa therapy | Spa therapy |
| Rest | | | | | |
| **½ hr**  **afternoon** | Exercise | Exercise | Exercise | Exercise | Exercise |
| **45 mins**  **afternoon** | TE | TE  with CD | TE | TE  with CD | TE  with CD |

TE: Therapeutic education

1. **Spa therapy programme (2 hrs/day)**

Staff in charge: Spa therapy physician and spa therapy technician

The patient is first of all assessed by the spa therapy physician.

Session plan:

- Hydrojet baths (or whirlpools): six 20-minute sessions in water at 38°.
- Massage shower: 10 minutes of manual massage underwater at 38°. The massage is followed by a 3-minute shower at 38°, performed remotely by the masseur. The strength of the massage and the jet must be specified by the spa therapy physician (gentle if the patient is experiencing intense pain and is apprehensive, more powerful if not).
- Directed mobilisation pool at 35°: 10 minutes of free bathing, 15 minutes of directed mobilisation by a qualified technician. This will be in the form of generic movements involving the entire spine and joints, as currently performed at these centres. Lumbar movements must include lumbar stretches.
- The spa therapy must be ended with the application of spa mud. The spa therapy physician must specify whether it will be applied directly to the skin or wrapped in a cloth (poultice). The temperature of the spa mud will be between 45° and 50° and the sessions will last between 15 and 20 minutes.

1. **Exercise programme (½ hour/day)**

Staff in charge: Physiotherapist

**2.1. Isometric strengthening of the spine (10 mins)**

- Lie with a cushion under the stomach, hands under the forehead and elbows apart.
- Lift the upper part of the torso, with the head aligned with the back.
- Hold for 6 seconds, repeat 5 times, resting for 6 seconds between each exercise.
- You can carry out 10 series of 5.

**2.2. Isometric strengthening of the abdomen (10 mins)**

- Lie on the back, arms crossed on the chest, legs bent at 90 degrees, with the feet flat and slightly apart.
- Lift the back to the middle of the shoulder blades while exhaling, with the head aligned with back.
- Hold for 6 seconds, repeat 5 times, resting for 6 seconds between each exercise.
- You can carry out 10 series of 5.

**2.3. Spinal-psoas-abdominal isometric co-contraction (10 mins)**

- Sit at a table, with the forearm flat and the feet flat and slightly apart.
- While exhaling, raise yourself up, rest the forearms on the table and lift a knee against the table top.
- Hold for 6 seconds, repeat 5 times, resting for 6 seconds between each exercise.
- You can carry out 10 series of 5.

1. **Group therapeutic education (45 mins/day)**

Staff in charge: Trained nurse or technician.

We will provide you with a CD on physical activity and rest, a second CD on work and a third CD on relaxation and pain management.

We advise you to put on the CDs for sessions 2, 4 and 5 (for a duration of 15 to 20 mins) and then discuss the messages transmitted in the CDs with the patients. Groups can include 4 to 6 patients.

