## IV - 3 - REQUIRED NUMBER OF SUBJECTS

The return-to-work rate at 1 year is estimated to be 70% in the control group. The hypothesis is to reach 80% in the intervention group. With a 5% risk and a power of 80%, a total of 600 patients are planned to be enrolled: 300 patients in the short spa therapy group and 300 patients in the control group. Taking into account the risk of loss-to-follow-up, 700 patients will be enrolled.

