# V – STUDY TREATMENT

## V - 1 – Intensive spa THERAPY

Standardisation of the intervention

A steering committee made up of rehabilitators, spa therapy physicians, rheumatologists, physiotherapists and psychotherapists from the various research sites and spa centres will be responsible for the preparation and standardisation of the intervention. This prior standardisation is essential to ensuring good reproducibility of the intervention during the study and the transfer of the intervention into routine clinical practice, if the trial demonstrates its efficacy.

Two meetings will be organised with all members of the steering committee to obtain a consensus on a therapeutic protocol, precisely describing the content and organisation of the intervention, taking into account the context and expertise of the various sites involved in the study.

Therapists

The various therapists responsible for the implementation of the intervention in this study will have a minimum of 5 years’ clinical experience. They will receive precise training in a specific meeting for the implementation of the intervention and they will receive a detailed manual describing the intervention and videos of each part of the intervention.

Content of the intervention

The patients in the intervention group will receive an intensive spa therapy consisting of the following, on a daily basis for five days:

- 2 hours of spa therapy (morning);
- 30 minutes of physical exercises (afternoon);
- 45 minutes of group therapeutic education (afternoon): two sessions dedicated to physical activity and rest (one of which with a CD), two sessions dedicated to work (one of which with a CD) and one pain-management session using a CD (45 minutes, all in the afternoon).

They will also receive a guide on lower back pain.

Treatment adherence assessment

Quantitative adherence (number and duration of sessions) and qualitative adherence (type of follow-up intervention, and method of performing the intervention) will be systematically assessed.

Tools for the future transfer of the intervention into routine clinical practice

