## IX -1- 5- Primary endpoint analysis

An intention-to-treat analysis will be carried out, i.e., all patients randomised will be analysed in their randomisation arm, regardless of the treatment received and any missing information. The bilateral tests will be carried out at the 5% threshold. The return-to-work rate percentage will be compared using the Chi-squared test.

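### Spa-arm education is given in groups of 4 to 6, but the planned tests and the sample size treat all patients as independent; if outcomes correlate within groups, spa-arm precision is overstated

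*Protocol*

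**What the plan says.** **Delivery.** Protocol sections V-1 and VII-2 give the spa arm, on each of five days, 2 hours of spa treatment, 30 minutes of exercises and 45 minutes of group education. Two of the five education sessions concern work. Annex III, item 3, adds that messages on the CDs are discussed with the patients and that "Groups can include 4 to 6 patients". Controls receive usual care organised by their own physicians (V-1, Comparator).

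**Primary analysis (IX-1-5).** "The return-to-work rate percentage will be compared using the Chi-squared test", two-sided at 5%, with all randomised patients in their assigned arm. No term for group, centre or site is named.

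**Secondary analyses (IX-1-6).** A linear mixed model has one random effect, on the patient, to handle repeated measurements. Pain area under the curve and Q-TWIST are compared by Mann-Whitney tests.

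**Sample size (IV-3).** The assumed one-year rates are 70% for control and 80% for spa. On that basis, "With a 5% risk and a power of 80%, a total of 600 patients are planned to be enrolled". Half of these go to each arm, and enrolment is raised to 700 to cover losses. No ICC or design effect appears.

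**The concern.** This is a partially nested design: individual randomisation, with groups formed afterwards in one arm only. Patients who share education sessions, including sessions about work, may have more similar return-to-work outcomes than patients from different groups. If so, the variance of the spa-arm rate is larger than the binomial variance that the Chi-squared test uses. The Mann-Whitney tests make the same assumption. The patient random effect does not help, because it models correlation between visits of one patient and not between patients of one group.

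At stake are the width of the interval for the primary comparison, the true level of a nominal 5% test, and the power stated in IV-3.

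**Working it through.** **Inputs from the Protocol:** 70% v 80%, 300 per arm, 700 enrolled (IV-3); two-sided 5% (IX-1-5); group size m = 4 to 6 (Annex III). **Assumption:** ICC 0.01 to 0.10, because the Protocol gives none.

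**Step 1. Reproduce the stated size.** For two independent proportions, with pooled variance under the null:

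n = [1.96·√(2·0.75·0.25) + 0.8416·√(0.21 + 0.16)]² / 0.10² = 293.2, so 294 per arm and 588 in total.

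This agrees with 300 and 600 after rounding up. The stated size thus contains no allowance for clustering beyond that rounding.

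**Step 2. Design effect, spa arm only.** DE = 1 + (m − 1)·ICC, from 1 + 3·0.01 = 1.03 to 1 + 5·0.10 = 1.50.

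**Step 3. True level of the unadjusted test.** With equal arms, the variance of the difference under the null grows by (1 + DE)/2, so

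α = 2·[1 − Φ(1.96 / √((1 + DE)/2))].

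**Step 4. Power of a test that uses the correct variance.**

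Power = Φ(0.10 / √((0.21 + 0.16·DE)/n) − 1.96).

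Worked example, m = 6, ICC 0.10, n = 300: √((0.21 + 0.24)/300) = 0.0387; 0.10/0.0387 − 1.96 = 0.62; Φ(0.62) = 73%.

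| m | ICC | DE | SE ratio √((1+DE)/2) | True α | Power, 300 per arm | Power, 350 per arm |
|---|---|---|---|---|---|---|
| any | 0 | 1.00 | 1.000 | 5.0% | 81.3% | 86.8% |
| 4 | 0.01 | 1.03 | 1.007 | 5.2% | 80.8% | 86.3% |
| 6 | 0.01 | 1.05 | 1.012 | 5.3% | 80.4% | 86.1% |
| 4 | 0.05 | 1.15 | 1.037 | 5.9% | 78.8% | 84.6% |
| 6 | 0.05 | 1.25 | 1.061 | 6.5% | 77.2% | 83.2% |
| 4 | 0.10 | 1.30 | 1.072 | 6.8% | 76.4% | 82.5% |
| 5 | 0.10 | 1.40 | 1.095 | 7.4% | 74.8% | 81.1% |
| 6 | 0.10 | 1.50 | 1.118 | 8.0% | 73.3% | 79.6% |

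With pooled null variance, power at 300 per arm is 80.9% without clustering and 72.0% in the last row, about one point lower.

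**Step 5. Check by simulation.** With beta-binomial groups, both arms at 70%, 300 per arm and 200,000 runs, the Chi-squared test rejected in 5.1% (m = 4, ICC 0.01), 6.1% (m = 5, ICC 0.05), 6.5% (m = 6, ICC 0.05) and 7.9% (m = 6, ICC 0.10). With no correlation it rejected in 5.0%.

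**Step 6. Where 80% power is lost.** Setting the Step 4 power to 80% with n = 300 gives DE = 1.076, so ICC = 0.076/(m − 1): about 0.025, 0.019 and 0.015 for m = 4, 5 and 6. With n = 350 and m = 6 the limit is about 0.095.

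**The case against.** **The ICC is unknown and may be small.** A reader might infer that the 5% level is exceeded as a matter of fact. The Protocol does not support that: it gives no ICC, and at 0.01 the excess is 0.2 to 0.3 points. Training, a manual, videos and CDs (V-1, Annex III) standardise delivery and should reduce differences between groups. This stands, and it is why the point is conditional.

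**Only the education has a stated group size.** A reader might infer that the whole spa programme is delivered in groups of 4 to 6 by the same staff. Annex III attaches that size to the education only: 45 of 120 + 30 + 45 = 195 minutes a day, or 5 × 45 = 225 minutes in all. The wording is permissive, and different staff are named for different components. This also stands. It argues for a lower ICC, not for zero.

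**Other features push the other way.** Randomisation is stratified by site (III-3), but the Chi-squared test is not. If sites differ equally in both arms, the test is conservative: simulated α is 4.8%, 4.6% and 3.4% for between-site SDs of 5, 10 and 20 points. In the direction that IX-3 spells out, missing spa outcomes count as failures and missing control outcomes as successes, which works against a false positive for spa. So the net level of the test cannot be read from the table. Neither feature corrects the spa-arm variance, however.

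**Decliners belong to no group.** III-4 cites 10% in an earlier trial. Treating 10% as singletons turns the highest DE into 0.9·1.50 + 0.1 = 1.45, and α into 7.7%. This is a small reduction.

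**Power has some reserve.** If outcomes are analysed for all 350 per arm, power stays at about 80% or more over the whole assumed range. This ignores any dilution from imputation.

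**A statistical analysis plan may handle it.** IX-1 promises one, and it is not shown. But the Protocol itself names the Chi-squared test and the patient-only random effect, and the point is about those.

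**Six spa centres.** A reader might infer a larger problem at centre level. With 300/6 = 50 spa patients per centre (equal split assumed) and a spa-specific centre ICC of 0.01, DE would be 1 + 49·0.01 = 1.49 and α 7.9%. The Protocol gives no ground for assuming centre effects confined to the spa arm, so this is not part of the conclusion.

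**Conclusion.** The point holds conditionally. The design creates possible clustering in one arm, and neither the named analyses nor the sample size allows for it. If the within-group ICC is positive, the standard error of the difference is understated by a factor of about 1.01 to 1.12 over the assumed range. The type I error from this source alone is then about 5.2% to 8.0%. Power is about 81% to 73% at 300 per arm, or about 86% to 80% at 350.

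These figures rest on an assumed ICC of 0.01 to 0.10, on every spa patient being in a full group of 4 to 6, and on no other departure from the simple model. At ICC 0.01 nothing of consequence changes. At 0.05 and above the loss of precision is worth reporting. It does not follow that the trial is underpowered or that its overall error rate exceeds 5%. The change is worth making because it is cheap and leaves the result almost unaltered if the ICC is near zero.

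**What to change.** 1. **Data.** Record each spa patient's centre and education group (start week) in the eCRF. The data listed in VII-1 and VII-3 include no group identifier. Adherence records and the start dates set by the centres may allow groups to be reconstructed, but that should not be relied on.
2. **Primary endpoint (IX-1-5).** Report the return-to-work risk difference with standard errors clustered on education group, treating controls and spa patients who do not attend as clusters of one, and accounting for the site strata. With 300 spa patients there would be about 300/6 = 50 to 300/4 = 75 groups, so clustering at group level is practicable.
3. **Secondary endpoints (IX-1-6).** Add a group random effect for the spa arm only to the mixed model. Beside the Mann-Whitney tests for pain area under the curve and Q-TWIST, give a difference in means with the same clusters.
4. **Sample size (IV-3).** State that 80% power assumes no within-group correlation, and give the range for the assumed ICCs: about 81% to 73% at 300 per arm, and about 86% to 80% at 350.

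**Cost.** One or two eCRF fields and some analysis wording. Intervals become slightly wider and the stated power slightly less favourable. No extra patients are needed and the intervention does not change.
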